### Statistical Analysis

Across the study population, outcomes will be assessed with descriptive statistics and compared between each ankle-foot device category as well as by PT intervention (ie, device-specific PT and standard of care). Inferential statistics for ordinal data will be conducted with a repeated-measures Friedman test (α=.05) and a Dunn post hoc test at a 95% CI. To address which measures are the most sensitive to intervention type, a linear mixed-effects model will be used. Separate models will be used for each type of measure (pain, subjective, cognitive, neurocognitive, functional, and biomechanical), and measures that have a significant association with the intervention type in the presence of adjusting (control) variables will be determined. Pair-wise comparisons will be tested for significance using linear contrasts with a Tukey honestly significant difference or by applying a Bonferroni correction, where applicable. The following sections outline the specific analyses that will be performed for each study objective.

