### Power Analysis and Sample Size Estimation

The sample size was based on a power analysis of 3 biomechanical measures (leading limb work, ground reaction force rate, and knee adduction moment rate) and 1 functional outcome (6MWT distance), and 1 subjective outcome (PEQ—utility) obtained from preliminary analyses, with all measurements obtained at baseline and 2 additional measurements over an 8-week period. The sample size was calculated for the group-by-time interaction, which tests the differences in change over time between the study groups. Assuming an α error rate of 5%, Table 5 presents the power achieved for each measurement for 30 participants, 15 (50%) in each group.

**Table 5 table5:** Power analysis and sample size estimation.

Measure	Difference, mean (SD)	Power (N=30)
Leading limb work (J/kg)	0.03 (0.04)	85
Ground reaction force rate (N/kg/s)	15 (26.9)	82
Knee adduction moment rate (N m/kg/s)	1.1 (1.2)	98
6MWT^a^ distance (m)	60 (61)	96
PEQ^b^—utility	8.4 (8.8)	96

^a^6MWT: 6-minute walk test.

^b^PEQ: Prosthesis Evaluation Questionnaire.

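### Which measures respond most to the intervention is to be decided by which are significant, but that tests each effect against zero and never one measure against another

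*Protocol article*

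**What the plan says.** The Statistical Analysis section of the protocol article sets a comparative aim: "To address which measures are the most sensitive to intervention type, a linear mixed-effects model will be used". The structure follows: "Separate models will be used for each type of measure (pain, subjective, cognitive, neurocognitive, functional, and biomechanical", closing the list of types. The criterion completes the sentence: "measures that have a significant association with the intervention type in the presence of adjusting (control) variables will be determined". Contrasts come next: "Pair-wise comparisons will be tested for significance using linear contrasts with a Tukey honestly significant difference or by applying a Bonferroni correction, where applicable". They are not described as contrasts between measures. Where the same sentence recurs in the section on biomechanical and functional outcomes, it follows models that compare ankle-foot conditions.

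The outcome-specific sections do not return to the comparative aim. The penalised regression in the pain section selects predictors of the PEQ pain score, which is another question. No common-scale effect, ranking with uncertainty or test between measures is stated.

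**The concern.** The question is which measures respond more than others. The stated rule asks, one measure at a time, whether the response differs from zero. These are different hypotheses. The measures are in different units and the models are separate by type, so nothing in the stated rule links, say, a pain score to a joint moment. Tukey or Bonferroni adjustment changes the threshold but not the null hypothesis.

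At stake is the reading of the result. Of two equally responsive measures, one may be reported as sensitive while the other is left out, and a reader may take the omission as evidence of insensitivity. Because the criterion is written down, this is not detail left to a fuller document.

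**Working it through.** **Inputs.** The Power Analysis section gives an alpha of 5%, power "for 30 participants, 15 (50%) in each group", and the target effect: "The sample size was calculated for the group-by-time interaction, which tests the differences in change over time between the study groups". Table 5 gives a difference, an SD and a power for five measures. Assumptions, because the article does not state them: a two-sided test; intervention type read as device-specific PT versus standard of practice; and the correlation between two measures, varied from 0 to 0.6.

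**Table 5's own powers.** With d = difference/SD, the two-sample t test has 28 degrees of freedom and noncentrality d × √(15/2) = 2.739 × d. In the order of Table 5, this gives 50.9, 31.4, 67.9, 73.9 and 71.4%, against the stated 85, 82, 98, 96 and 96%. Other readings match single cells, but none matches all five:

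- paired test with n=30: 97.8, 83.9, 99.8, 99.9, 99.9%
- 30 per arm (normal approximation): 82.8, 57.9, 94.4, 96.8, 95.9%
- group-by-time F test over three visits, f = d/2, within-person correlation 0: 88.3, 63.0, 97.4, 98.8, 98.3%

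The within-person correlations are not given, so both sets of powers are carried forward.

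**Chance of different labels for two equally sensitive measures.** If each has power p and they are independent, exactly one is significant with probability 2p(1−p). For example, at p = 0.82 this is 2 × 0.82 × 0.18 = 0.295, and at p = 0.509 it is 2 × 0.509 × 0.491 = 0.500. For correlated measures it is 2(p − p₁₁), where p₁₁ is the bivariate normal probability that both are significant. Each row below is a pair of measures that both have that row's effect.

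| Measure | d | Stated power | Different labels, correlation 0 / 0.5 | t-test power | Different labels, correlation 0 / 0.5 |
|---|---|---|---|---|---|
| Leading limb work | 0.03/0.04 = 0.750 | 85% | 25.5% / 18.5% | 50.9% | 50.0% / 33.3% |
| Ground reaction force rate | 15/26.9 = 0.558 | 82% | 29.5% / 21.0% | 31.4% | 43.1% / 29.3% |
| Knee adduction moment rate | 1.1/1.2 = 0.917 | 98% | 3.9% / 3.3% | 67.9% | 43.6% / 29.6% |
| 6MWT distance | 60/61 = 0.984 | 96% | 7.7% / 6.2% | 73.9% | 38.6% / 26.6% |
| PEQ utility | 8.4/8.8 = 0.955 | 96% | 7.7% / 6.2% | 71.4% | 40.9% / 28.0% |

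A simulation of 40,000 trials per setting with two-sample tests agrees. For d = 0.56, 0.75, 0.92 and 0.98 it gives 43, 50, 43 and 39% at correlation 0, and 27, 30, 27 and 24% at correlation 0.6.

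**Unequal effects.** With independent measures and true effects of 0.92 and 0.75, the weaker alone is flagged in 0.509 × (1 − 0.679) = 16% of trials, and the stronger alone in 0.679 × (1 − 0.509) = 33%.

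**Direct comparison.** In simulation, a contrast of the two standardised effects separates equal measures in about 6-8% of trials. Where the significance labels differ, that contrast is itself significant in only about 12-17% of cases.

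**The case against.** The case for leaving the plan alone has four parts.

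First, ranking measures is not among the three study objectives, and the sentence sits in an overview paragraph. This stands, and it limits the weight of the point. A reader might infer that a list of sensitive measures will be carried into later work or into the preliminary guidelines. The article does not say so. Nor does it say that a non-significant measure will be called insensitive.

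Second, mixed models yield estimates, and reporting standardised effects with intervals could be left to a fuller analysis plan. This stands for the reporting, but not for the criterion: significance is named as the rule that answers the question.

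Third, the larger percentages rest on two-sample powers well below those in Table 5, and the simulated test is simpler than the planned adjusted model with three visits. This stands. At the stated powers the effect is small (4-8%) for the three measures at 96-98%. It would be wrong to infer that Table 5 is in error, because unstated within-person correlations could explain the gap. It would also be too strong to say that the list is mostly noise: in the unequal example the stronger measure is the one singled out about twice as often (33% against 16%).

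Fourth, a direct comparison has little power with 30 participants: 14-22% for effects of 0.56 against 0.98 in simulation. This also stands. It shows how little the data can rank measures, which a list of significant measures conceals.

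**Conclusion.** The point holds. The stated criterion does not answer the stated question, and nothing in the outcome-specific sections repairs it. That conclusion is logical and does not depend on Table 5.

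Its size does depend on power. For equally sensitive independent measures, different labels arise in about 4-30% of trials at the stated powers, and in about 39-50% if Table 5's ratios are two-sample standardised effects. The second range falls to 24-30% at correlation 0.6. The correlations between measures and the two-sided test are assumptions. Table 5 covers five selected measures, and the power for the many others is not given.

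**What to change.** For each measure, report the standardised intervention effect (the model contrast divided by the SD of change) with a confidence interval. Say that one measure is more sensitive than another only on the basis of an interval for the difference in standardised effects, and label any ranking exploratory.

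Obtain that interval from a joint model, or by resampling participants within arm only with a small-sample correction. A plain percentile bootstrap within arm and site should be avoided: 30 participants over 3 sites and 2 arms leaves about 5 per cell. In a simulation of 1,500 trials with 600 resamples each, it declared equal measures different in 8-12% of trials.

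If this is not wanted, reword the aim to ask which measures show an association with the intervention, and state that non-significant measures are not to be read as insensitive.

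The cost is a little more analysis on data already planned. At N=30 few pairs of measures will be separable, so there will be fewer firm statements about which respond most.

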### Planned Statistical Analysis for Biomechanical and Functional Outcomes

Although there are numerous biomechanical and physiological parameters that can be evaluated following gait analysis [61], this investigation will focus on the biomechanical parameters that are most relevant, commonly used, able to discriminate, and have specific clinical relevance for individuals with transfemoral limb loss. The primary biomechanical outcome measures will include measures of rollover shape, individual characteristics of the 3D ground reaction force, and ankle, knee, and hip joint angles, moments, and powers (on both the intact and affected limbs). To evaluate the load distribution of the medial and lateral knee compartments, the peak resultant ground reaction force, ground reaction force rate, peak knee external adduction moments, and knee external adduction moment rate will be compared between the baseline (passive energy storing and returning condition) and the powered condition at each follow-up visit.

Linear mixed-effects models will be used to identify statistically significant differences in gait temporal-spatial and biomechanical variables for all walking speeds. The fixed effects will be the average differences in gait biomechanical and temporal-spatial variables by prosthetic ankle type (powered vs passive). These models also estimate random effects because of differences in mean biomechanical variables across participants, as well as the random effects associated with minimized variability, as the participants will be tested with both prostheses. For example, a linear mixed-effects regression will be used to examine the relationship between the intact knee peak external adduction moment and the prosthetic ankle-foot condition. Peak intact knee external adduction moment will be the dependent variable, whereas ankle-foot condition will be the independent variable, and participant-by-ankle-foot condition will be modeled as random effects. Pair-wise comparisons will be tested for significance using linear contrasts with a Tukey honestly significant difference or by applying a Bonferroni correction, where applicable. In addition, linear mixed-effects regression will be used to determine the association between prosthetic peak ankle power and foot condition.

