### Baseline Visit

#### Informed Consent, Enrollment, and Randomization

Informed consent for each potential participant will be conducted in person in a private room. The site-principal investigator or qualified designee will explain the study protocol in detail. The participants will be asked to consent to randomization of the treatment group, either to be fit with the powered ankle-foot device and receive device-specific PT (group A) or to be fit with the powered ankle-foot device and receive the current standard of practice that does not include device-specific PT (group B). The participants will be asked to make a commitment to be available for all study-related activities. The individuals will be given adequate time to review and comprehend all information about the study before agreeing to participate, minimizing the possibility of coercion and undue influence. After the study has been explained and consent has been given, the participants will be randomized into the 2 groups using a computer-generated algorithm that block randomizes participants into each group at each site.

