### Planned Statistical Analysis for Pain Outcomes

The following parameters will be measured and statistically compared between baseline (energy storing and returning condition) and each follow-up visit with the powered ankle-foot prosthesis (weeks 4 and 8):

Joint reaction forces on the lower back (L5 and S1) and contralateral (intact) kneesPEQ pain scoresFunctional outcome measures (6MWT, AMPpro, and CHAMP)

Spearman correlations will be calculated to correlate data between pain and lower extremity kinematic and kinetic parameters of interest and pain and functional outcome values across the groups. Linear mixed-effects models will be used to identify statistically significant differences in pain scores and biomechanical variables listed in the previous section for all walking speeds. For example, a linear mixed-effects regression will be used to examine the relationship between peak reaction moments at L5 and S1 and pain for each prosthetic ankle-foot condition. Pair-wise comparisons will be tested for significance using linear contrasts with a Tukey honestly significant difference or by applying a Bonferroni correction, where applicable.

Multiple linear regression will be performed with PEQ pain as the dependent variable. Because of the large number of predictor variables in relation to the number of participants, penalized methods (eg, ridge regression or lasso) will be used to identify variables that contribute the most to the prediction model. Penalized methods add a tuning parameter to the regression model that shrinks the less important coefficients toward 0. Cross-validation will be used to select the best tuning parameter value [62]. The independent variables will be comprised of functional parameters (eg, peak joint reaction forces) and the condition (ankle-foot type and intervention).

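### The trial is sized on the group-by-time interaction, but no planned model names that term, and the detailed gait and functional analyses leave out the randomised arm

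*Protocol article*

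**What the plan says.** All references are to the protocol article.

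- **Power Analysis and Sample Size Estimation:** "The sample size was calculated for the group-by-time interaction, which tests the differences in change over time between the study groups". Table 5 gives power "for 30 participants, 15 (50%) in each group" for leading limb work, ground reaction force rate, knee adduction moment rate, 6MWT distance and PEQ utility.
- **Planned Statistical Analysis for Biomechanical and Functional Outcomes:** "The fixed effects will be the average differences in gait biomechanical and temporal-spatial variables by prosthetic ankle type (powered vs passive". In the worked example, on the intact knee adduction moment, ankle-foot condition is the sole independent variable. The knee-loading measures, which include two of the sizing measures, are compared between baseline and the powered condition at each follow-up.
- **Planned Statistical Analysis for Pain Outcomes:** PEQ pain, 6MWT, AMPpro and CHAMP are "statistically compared between baseline (energy storing and returning condition) and each follow-up visit with the powered ankle-foot prosthesis (weeks 4 and 8". A separate penalised regression of PEQ pain lists ankle-foot type and intervention among its predictors.
- **Planned Statistical Analysis for Cognitive Load and Neurocognitive Outcomes:** ankle-foot type and PT intervention are both fixed effects.
- **Statistical Analysis (general paragraph):** outcomes will be compared by device and by PT intervention, and mixed models for each class of measure will look for association with intervention type. Also, "Inferential statistics for ordinal data will be conducted with a repeated-measures Friedman test".

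**The concern.** Study Objectives lists the effect of the PT intervention as part of the second objective, and A versus B is the only contrast that randomisation protects. The Study Overview relies on that contrast to separate device effects from rehabilitation effects.

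Ankle type cannot do this job. Both arms move from passive to powered between baseline and week 4 and stay powered to week 8, so ankle type is the same variable as before/after in every participant. If the detailed sections are followed as written for gait and function, the quantity that justified 30 participants is not estimated there. A reader could also take a significant ankle-type coefficient as evidence on the rehabilitation programme.

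**Working it through.** **1. The plan's own figures.** Table 5 gives power of 85, 82, 98, 96 and 96% with "Assuming an α error rate of 5"%. The article gives neither the within-person correlation nor what the SD refers to. If the SD is that of change, a two-sided two-sample comparison at 15 per arm, power = Φ(d·√(15/2) − 1.96), gives:

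| Measure | d = difference/SD | Power obtained | Table 5 |
|---|---|---|---|
| Leading limb work | 0.03/0.04 = 0.75 | 54% | 85% |
| Ground reaction force rate | 15/26.9 = 0.56 | 33% | 82% |
| Knee adduction moment rate | 1.1/1.2 = 0.92 | 71% | 98% |
| 6MWT | 60/61 = 0.98 | 77% | 96% |
| PEQ utility | 8.4/8.8 = 0.95 | 74% | 96% |

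A paired t test in all 30 gives 98, 84, 99.8, 99.9 and 99.9%. Neither reproduces the table, and nothing below depends on reproducing it. The comparison does show that a pooled before-after test and a between-arm test of change are far apart in power on the same inputs.

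**2. What the ankle-type coefficient estimates.** With equal arms it is the mean of the two arms' changes, (Δ_A + Δ_B)/2.

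- Δ_A = 60 m, Δ_B = 0 m: (60 + 0)/2 = 30 m. The interaction is 60 − 0 = 60 m.
- Δ_A = 30 m, Δ_B = 30 m: (30 + 30)/2 = 30 m. The interaction is 30 − 30 = 0 m.

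The coefficient is the same whether PT works as the planners assumed or does nothing. A participant-by-condition random effect would absorb the extra spread in the first case but would not attribute it to the arm.

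**3. What an intervention term estimates, by coding.**

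- *Assigned group, main effect over three visits.* Randomised arms do not differ in expectation at baseline, so the term targets (0 + 60 + 60)/3 = 40 m, two-thirds of the follow-up difference.
- *PT received, zero for everyone at baseline, alongside ankle type.* The term is then a post-baseline contrast, close to the interaction and not diluted in this way.

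The article does not say which coding is meant.

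**4. Illustration of the first coding.** Assume 61 m is the SD of change and compound symmetry with correlation ρ. Then σ = 61/√(2(1−ρ)), and the SD of a three-visit mean is σ·√((1+2ρ)/3). Power is from the non-central t, 15 per arm.

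| ρ | SD of 3-visit mean | Power for 40 m |
|---|---|---|
| 0.5 | 49.8 m | 57% |
| 0.7 | 70.4 m | 32% |
| 0.8 | 89.8 m | 22% |

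Under the same assumptions the A-minus-B difference in average change has SD 61·√0.75 = 52.8 m and power 85%.

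**5. Friedman test.** It ranks visits within each participant. It has one within-person factor and no place for a between-person factor, so neither the arm nor arm-by-visit can enter.

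**The case against.** The strongest reply is that the randomised comparison is in the plan. The general paragraph promises a comparison by PT intervention and mixed models for intervention type in every class of measure, functional and biomechanical included. Intervention is also in the PEQ pain regression and the cognitive models. This stands: a reader might infer that the PT effect is tested nowhere, and the article does not support that. What it lacks is the interaction itself, and its general and detailed sections describe different models for the same gait outcomes.

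Second, ankle type is the natural term for objective 1, powered versus passive. That also stands, and the model should be kept for that purpose. It does not serve objective 2.

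Third, a condensed article may leave model terms and coding to a fuller document. That covers omissions. Here the article states its fixed effects and its ordinal test, and they do not match its own sizing.

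Three further inferences should be resisted:

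- *That power is really 57% or 32%.* These figures require main-effect coding, an assumed correlation and an assumed meaning of the SD. The same assumptions give 85%, not Table 5's 96%, for the average-change contrast, so they do not recover the planners' inputs.
- *That Table 5 is wrong.* Too few inputs are printed to decide.
- *That leaving out site inflates the standard error.* Randomisation "block randomizes participants into each group at each site", and the laboratories differ in equipment and examiner, but a constant site offset cancels from each participant's change. The adjustment variables under Limitations are also given only as examples.

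Finally, the Friedman test applies to ordinal data only and does not touch the five Table 5 measures as continuous or visual-analog scores.

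**Conclusion.** The point holds in this form: the group-by-time interaction used for sizing is specified in no planned model, and the detailed gait, functional and PEQ pain comparisons estimate a pooled before-after change. As written, those analyses cannot estimate the PT contrast of objective 2. This follows from the design and the stated terms alone, without any assumption about variance or correlation.

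The intervention terms elsewhere may or may not repair this, depending on an unstated coding. If they are group main effects over three visits, they target two-thirds of the follow-up difference. That fraction assumes equal arms at baseline and the same difference at weeks 4 and 8. For ordinal outcomes, the named test leaves the arm out altogether.

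**What to change.** - Keep the ankle-type model and label it as the analysis for objective 1, a before-after comparison.
- For objective 2, fit for each continuous outcome a mixed model with group, visit (baseline, week 4, week 8), group-by-visit and a participant random effect. Report the A-minus-B difference in change at week 4 and at week 8, with confidence intervals, as the PT effect.
- Where an intervention term is retained in other models, state how it is coded at baseline.
- For ordinal outcomes, add a between-arm analysis of change: an ordinal mixed model or a rank test on change scores.
- Site may be added because it is the randomisation stratum, but no gain in standard error should be claimed for the change contrast.

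The cost is revised statistical wording and a few degrees of freedom. It needs no new data, and the planned 30 participants are unchanged.
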